|  | 
stay in patient subgroups in selected centers, with and without censoring at 90 days
 
 
- The presence or absence of new kidney injury during ICU stay, and duration and recovery herefrom, with and without censoring at 90 days
 
- The need for new initiation of renal replacement therapy in ICU (incidence, duration and recovery hereof), with and without censoring at 90 days
 
- The need for hemodynamic support during ICU stay, its duration and the time to (live) weaning from hemodynamic support, with and without censoring at 90 days
 
- The incidence of new-onset atrial fibrillation and recurrence of pre-existing atrial fibrillation during ICU stay in selected centers, with and without censoring at 90 days
 
- The incidence of major adverse cardiovascular events (MACE; non-fatal myocardial infarction, non-fatal stroke, low cardiac output syndrome, and cardiovascular death) during ICU stay in selected centers, with and without censoring at 90 days
 
- The presence or absence of signs of liver dysfunction in ICU, with and without censoring at 90 days
 
- The duration of antibiotic treatment during ICU stay, with and without censoring at 90 days
 
- The incidence of bacteremia, and of airway, urinary tract, wound and other infections acquired during ICU stay, with and without censoring at 90 days
 
- Peak and time profile of C-reactive protein concentrations during ICU stay, with and without censoring at 90 days
 
- The number of readmissions to the ICU within 48 hours after discharge, with and without censoring at 90 days
 
- The presence or absence of delirium during ICU stay (in selected centers), with and without censoring at 90 days
 
- Biochemical, metabolic, immunological, inflammatory, cardiac and (epi)genetic markers on blood and tissue samples up to 4 years post randomization (depending on additional funding and in selected centers)
 
- Muscle strength, rehabilitation, recovery of organ function and survival up to 4 years post randomization in selected centers and subgroups of patients (depending on additional funding)
 
- Long-term functional outcome:
 
 |

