- The need for pharmacological or mechanical hemodynamic support during ICU stay and its duration, with and without censoring at 90 days. In addition, time to final (live) weaning from all pharmacological or mechanical support will be analyzed (with and without censoring at 90 days), with ICU non-survivors censored beyond the longest duration of pharmacological or mechanical hemodynamic support of the survivors.
- The incidence of new-onset atrial fibrillation and recurrence of pre-existing atrial fibrillation during ICU stay in selected centers, with and without censoring at 90 days. In order to quantify and phenotype burden of atrial fibrillation, we will perform a detailed analysis of atrial fibrillation occurrence, including timing of onset, duration and number of episodes. Strategies regarding medical and/or electrical rhythm control, as well as rate control will be documented.
- The incidence of major adverse cardiovascular events (MACE; non-fatal myocardial infarction, non-fatal stroke, low cardiac output syndrome, and cardiovascular death) during ICU stay in selected centers, with and without censoring at 90 days
- The presence or absence of signs of liver dysfunction in ICU, with and without censoring at 90 days: cholestatic liver dysfunction, cytolytic liver dysfunction.
- The duration of antibiotic treatment during ICU stay, with and without censoring at 90 days
- The incidence of bacteremia, airway, urinary tract, wound and other infections (all with and without censoring at 90 days).
- Inflammation: the effect of the intervention on markers of inflammation will be analyzed by comparing the distribution of the highest value of C-reactive protein during ICU stay and changes from baseline to the highest value and by comparing time profiles of daily C-reactive protein values (with and without censoring at 90 days).
- The number of readmissions to the ICU within 48 hours after discharge (with and without censoring at 90 days)
- The presence or absence of delirium during ICU stay (in selected centers), with and without censoring at 90 days. To that purpose, the worst Intensive Care Delirium Screening Checklist (ICSDC) score observed per day in ICU will be entered in the database.
- Biochemical, metabolic, immunological, endocrine, inflammatory, cardiac and (epi)genetic markers on blood and tissue samples up to 4 years post randomization (depending on additional funding and in selected centers)

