  - History of stroke (Y/N) (cerebrovascular accident (CVA) and/or transient ischemic attack (TIA)) (selected centers)
  - Cerebrovascular disease with mild or no disability
  - Hemiplegia
  - Paraplegia
- History of active malignancy (last 5 years):
  - Solid tumor without metastasis (Y/N)
  - Metastatic cancer (Y/N)
  - Hematological malignancy (Y/N)
- Chronic neuroleptics (Y/N)
- AIDS (not just HIV-positive) (Y/N)
- Peptic ulcer disease (Y/N)
- Connective tissue disease (Y/N)
- Immune suppressed status
  - Neutropenia (<1000 neutrophils/mm^3)
  - corticosteroid therapy (prednisolone or equivalent >0.5 mg/kg/day for >3 months)
  - systemic corticosteroid therapy <3 months (lower dose)
  - chemotherapy within one year
  - radiotherapy within one year
  - bone marrow recipient
  - solid organ transplant recipient
  - immunosuppressive drug for auto-immune diseases
  - congenital immunodeficiency
- life style risk factors
  - tobacco use (>20 pack years)
  - alcohol abuse (>1L of wine /day or equivalent = 10g alcohol day)
  - IV drug abuse
- Insulin drip at admission (Y/N)
- Lowest plasma creatinine in 3 months period before ICU admission
- Last plasma creatinine before randomization (maximum 24 hours before ICU admission)
- Renal replacement therapy pre-admission (Y/N), chronic renal replacement therapy (Y/N)
- Blood glucose concentration on admission
- Blood lactate on admission
- Investigation site
- Investigation ID
- Check for inclusion criteria

- Adult patient ( $\geq 18$  years of age)
- Check for exclusion criteria
  - Do not resuscitate (DNR) order or moribund (expected to die within 12 hours) at ICU admission
  - Patient able to receive oral feeding
  - No arterial line or central venous line needed
  - Previous inclusion in the trial
  - Enrolled in another outcome randomized controlled trial (RCT)
  - Transfer from a non-participating ICU with a pre-admission ICU stay  $>7$  days
  - Planned to receive early parenteral nutrition (i.e. during the first week in ICU)
  - Diabetic ketoacidotic or hyperosmolar coma on ICU admission
  - Inborn metabolic diseases
  - Insulinoma
  - Known to be pregnant or lactating
- Informed consent (patient or relative)

A separate log file will be kept for the patients who were not included in the study. These data will not be used for analysis, but are required to construct an adequate patients' flow diagram (CONSORT diagram). Only the following data will be recorded:

- Hospital ID number
- Age, gender

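### The yes/no endpoint on hemodynamic support is not limited to support newly started after randomisation, so patients already on it are fixed events in both arms and dilute the comparison

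*Protocol*

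**What the plan says.** Section 1 lists "The need for hemodynamic support during ICU stay, its duration and the time to (live) weaning from hemodynamic support". Section 3.3 has "The need for pharmacological or mechanical hemodynamic support during ICU stay and its duration" and adds time to final live weaning, with ICU non-survivors censored beyond the longest duration among survivors. Neither place says that the support must be new or must start after randomisation, and section 13 (Data handling) adds no such rule. Liver dysfunction is worded in the same open way: "The presence or absence of signs of liver dysfunction in ICU, with and without censoring at 90 days: cholestatic liver dysfunction, cytolytic liver dysfunction".

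Neighbouring endpoints are limited:

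- Kidney: "The presence or absence of new kidney injury during ICU stay".
- Renal replacement therapy: "The need for new initiation of renal replacement therapy in ICU (incidence, duration and recovery hereof"). Section 13 supports this with a baseline item, "Renal replacement therapy pre-admission (Y/N), chronic renal replacement therapy (Y/N").
- Infection: section 13 counts a new infection only if antimicrobials began after randomisation and beyond the first 48 hours in the ICU.
- Major adverse cardiovascular events: section 13 leaves out events that were present on admission or were the admission diagnosis.

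**The concern.** Section 2 describes critical illness as continuous dependency on mechanical or pharmacological support of vital organs, so some patients will be on hemodynamic support when they enter. Under section 6.1, allocation follows within two hours of admission. Section 5.4 also lets patients who were not critically ill at admission be included later, once they worsen. For anyone on support at randomisation, the answer to whether support was needed during the ICU stay is already yes. These patients add events to both arms but no information on treatment.

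The risk is that a real benefit or harm on new circulatory failure appears as a risk ratio close to 1 with a non-significant test. Section 3.1 says the trial is two-tailed so that it can also detect harm, and a null result on this item would be hard to interpret.

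The Protocol recognises the problem for one organ. Section 13 notes that patients may arrive with renal function already altered and adds an evaluation from randomisation onward. It does nothing comparable for hemodynamic support.

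**Working it through.** **Is there a figure to reproduce?** No. The Protocol gives no event rate, effect size or power for this endpoint, so what follows is an illustration.

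**Inputs from the Protocol.** Total 9230 patients (section 9.1), allocated 1:1 (section 5.4), so N = 9230 / 2 = 4615 per arm. Significance is at 0.05 without correction for multiple testing (section 9.3), taken here as two-sided.

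**Assumed inputs, not in the Protocol.** New need for support in patients free of it at randomisation: q = 20% v 17%. Share already on support at randomisation: b = 20%, 40% or 60%. Treatment acts only on new need.

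**Formulas.**

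- Rate as worded: p = b + (1 − b)q.
- Power: Φ(d / SE − 1.96), where d is the difference in rates and SE = √[(p₀(1 − p₀) + p₁(1 − p₁)) / n].
- As worded, n = 4615. For new need in patients at risk, the rates are 20% and 17% and n = 4615(1 − b).

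**Worked case, b = 20%.**

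- As worded: p₀ = 0.20 + 0.80 × 0.20 = 0.360 and p₁ = 0.20 + 0.80 × 0.17 = 0.336. RR = 0.336 / 0.360 = 0.93. SE = √[(0.2304 + 0.2231) / 4615] = 0.0099. d / SE = 0.024 / 0.0099 = 2.42. Power = Φ(0.46) = 68%.
- New need, at risk: n = 4615 × 0.80 = 3692. SE = √[(0.1600 + 0.1411) / 3692] = 0.0090. d / SE = 0.030 / 0.0090 = 3.32. Power = Φ(1.36) = 91%. RR = 0.17 / 0.20 = 0.85.

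| On support at randomisation | As worded | RR | Power | New need, at risk: n per arm | RR | Power |
|---|---|---|---|---|---|---|
| 20% | 36.0% v 33.6% | 0.93 | 68% | 3692 | 0.85 | 91% |
| 40% | 52.0% v 50.2% | 0.97 | 41% | 2769 | 0.85 | 82% |
| 60% | 68.0% v 66.8% | 0.98 | 23% | 1846 | 0.85 | 65% |

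The restricted comparison has more power although its denominator is smaller.

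**Is the gain only a matter of dropping patients?** No. If new need is counted over all 4615 per arm, the rates at b = 20% are 16.0% v 13.6%. The absolute difference is the same 2.4 points as worded, RR is 0.85 and power is 90%. At 40% and 60% on support, power is 79% and 60%. The fixed events add variance to the comparison, and removing them recovers the power.

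**The case against.** The strongest reply is that any need during the ICU stay, in all randomised patients, is a valid intention-to-treat comparison. Randomisation should balance prior support, so neither arm is favoured. That stands: what is lost is sensitivity. A reader might infer that the result would be biased between arms; nothing in the Protocol supports that.

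Second, the endpoint is a bundle. Patients on support at entry are informative for duration and for time to live weaning, so only the yes/no part is affected. That also stands.

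Third, the cardiovascular-event endpoint already covers part of new circulatory failure, because low cardiac output there includes need for inotropic or mechanical circulatory support not present on admission. This is a partial safeguard. It applies in selected centers only and does not cover every form of hemodynamic support.

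Fourth, the renal rule may have a reason of its own, since chronic renal replacement therapy exists, and some other secondary endpoints, such as delirium and tracheostomy, also lack a limit to new events. The difference from the kidney endpoints is therefore not an error in itself. It shows that the Protocol has a workable rule it could extend.

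Fifth, handling of baseline status is often left to the statistical analysis plan, which is not at hand. But the endpoint and the list of recorded items are fixed in the Protocol, and that list has no item for hemodynamic support at randomisation.

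A reader might also infer that patients with cirrhosis or a liver transplant are equally fixed events for liver dysfunction. The Protocol does not support this. It gives no threshold for cholestatic or cytolytic dysfunction, and neither condition alone guarantees abnormal tests.

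**Conclusion.** The point holds for the yes/no component of one secondary endpoint. As worded, patients on hemodynamic support at randomisation are events regardless of treatment, the risk ratio moves toward 1 and precision falls. The direction follows for any share above zero, provided treatment acts on new need.

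The size rests wholly on assumed rates. With 20% to 60% on support at entry and new need of 20% v 17%, RR 0.85 is seen as 0.93 to 0.98, and power is about 68% to 23% instead of about 91% to 65%. The trial is not powered on this endpoint, and its primary and safety conclusions are untouched. For liver dysfunction the same reasoning is plausible, but the Protocol offers nothing from which to size it. This is an inexpensive improvement that should be made.

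**What to change.** In sections 1 and 3.3, define the yes/no comparison as new initiation of pharmacological or mechanical hemodynamic support after randomisation, in patients not on it at randomisation. Take status at randomisation from time-stamped data in the patient data management system, which section 13 says will be kept. Report any need during the ICU stay in all randomised patients as a descriptive figure. Keep duration and time to live weaning for all patients.

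For liver dysfunction, separate what is present at randomisation from what newly arises, where admission liver tests exist. Section 6.3 leaves these tests to local practice.

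Costs: the denominator of the yes/no test is smaller. Some extra extraction is needed, because the drug item in the case record form is a cumulative daily dose and cannot by itself separate use before and after allocation on the first day. Patients on support at entry who are weaned and later need it again drop out of the yes/no test.

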## 2. Background and rationale

**Critical illness** is a life-threatening medical condition that is induced by severe medical illnesses, major trauma or extensive surgeries and is characterized by a continuous dependency on mechanical and/or pharmacological vital organ support, without which death would ensue. Thanks to advances in intensive care medicine, patients now usually survive such conditions that were previously lethal. However, in spite of this progress, about 25% of patients do not recover swiftly from the acute condition. These so-called “prolonged critically ill patients” remain dependent on intensive care for weeks to months. With each day in intensive care, risk of death rises further and survivors have an important long-term legacy (1). The costs for society of intensive care are enormous and predominantly driven by the duration of intensive care stay and by infectious complications (2).

Elevated blood glucose levels (hyperglycemia) are present in virtually every adult patient in the ICU, and the degree of hyperglycemia is related to the risk of adverse outcome (3, 4). Currently, **controversy exists on whether targeting normal blood glucose levels with insulin therapy, referred to as “tight blood glucose control” (TGC), as compared with tolerating hyperglycemia, improves outcome of these patients.** In 3 well designed single center RCTs,

the coordinator (KU Leuven) of this study has demonstrated that morbidity, mortality, use of healthcare resources and long-term functional status significantly improved with TGC (5-10). In particular, the duration of dependency on intensive medical care was reduced substantially. Rapidly, many centers worldwide adopted TGC as part of the standard of care. However, a subsequent large pragmatic multicenter RCT found increased mortality with TGC attributable to more hypoglycemia (low blood glucose levels) (11, 12). Current practice guidelines still recommend some degree of glucose control, but controversy remains about its benefit (13-15) and local practices vary widely in Europe and the rest of the world (16). Irrespective of the degree, blood glucose control is difficult and is time and resource consuming. Two differences between the pioneer studies and the generalizability trial may explain the different results: in the pioneer studies, TGC was performed by expert and extensively trained nurses, which resulted in safer blood glucose control, and early intravenous feeding was used for all patients when enteral feeding was not reaching the caloric goals (table 1). Consortium members have subsequently shown in multicenter RCTs that not using early intravenous feeding improves outcome, with less infectious complications and faster recovery (17, 18). **Hence, it currently remains unknown whether TGC, applied with optimal tools to avoid hypoglycemia, is beneficial without early intravenous feeding.**

**Table 1: Comparison of landmark trials on blood glucose control in critically ill patients**

|                           | Pioneer studies (Leuven)                                                                                                                                                                                  | NICE-SUGAR                                                                                                                                                                                                                          |
|---------------------------|------------------------------------------------------------------------------------------------------------------------------------------------------------------------------------------------------------------|--------------------------------------------------------------------------------------------------------------------------------------------------------------------------------------------------------------------------------------------|
| Number of patients | 3448                                                                                                                                                                                                             | 6100                                                                                                                                                                                                                                       |
| Population         | Critically ill adults and children                                                                                                                                                                               | Critically ill adults                                                                                                                                                                                                                      |
| Effect of TGC      | Reduced morbidity
Reduced mortality
Reduced long-term legacy
Reduced healthcare costs                                                                                                                   | Increased mortality
No effect on morbidity                                                                                                                                                                                              |
| Strengths          | 
 
- Accurate glucose measurements, highly standardized
 
- Standardized protocol by extensively trained nurses, low incidence of hypoglycemia
 
 | 
 
- Multicenter
 
- Pragmatic, “real life” and thus not standardized context
 
                                                                                                        |
| Weaknesses         | 
 
- Nutritional strategy comprised the use of early parenteral nutrition, later shown to be harmful
 
                                                       | 
 
- Inaccurate glucose measurements
 
- Un-validated “if-then” algorithm, with <50% of measurements within target and high incidence of hypoglycemia
 
 |

 The performance of the protocol has been improved further by the LOGIC-Insulin software.

The **aim of TCG-fast** is to compare the effectiveness of TGC versus tolerating hyperglycemia in adult critically ill patients of both sexes **who are not receiving intravenous nutrition for up to one week in the ICU**. To this purpose, we will perform a multicenter RCT that is adequately powered for patient-centered and economic endpoints. Patients will be randomly allocated to TGC to target normal fasting glucose levels with insulin versus tolerating hyperglycemia up to a predefined level. TGC will be guided by our previously developed computer algorithm that has shown even to outcompete the well-trained nurses, with virtually preventing hypoglycemia (LOGIC-Insulin) (19). The efficacy and safety of the LOGIC-Insulin algorithm has been confirmed in a multicenter context by members of this consortium (20).

### 3. Trial objectives and design

#### 3.1 Trial objectives

The main objective of this study is to test the hypothesis that in adult critically ill patients receiving an evidence-based, restrictive feeding regimen (no parenteral nutrition in the first week of critical illness), targeting normal blood glucose concentrations (80-110 mg/dl) reduces short-term morbidity and dependency on intensive care as compared with tolerating hyperglycemia up to 215 mg/dl. The null hypothesis is that there will be no difference in the primary outcome measures (incidence of new infections during ICU stay, ICU length of stay and the time to live discharge from ICU) between the two strategies. The study is two-tailed so that it is also powered to detect a negative impact of targeting normal blood glucose concentrations. As a safety endpoint, mortality will be monitored. These analyses will be done unadjusted as well as adjusted for risk factors.

The secondary objectives are:

- To study the long-term impact of the intervention (morbidity and mortality)
- To study the economic impact (healthcare resources)
- To study the underlying mechanisms that may explain an eventual benefit (or harm) from targeting normal blood glucose concentrations with intensive insulin therapy (depending on additional funding). This will be achieved by studying the effects of treatment allocation on metabolic, endocrine, inflammatory, coagulation, cardiac and (epi)genetic markers in blood and tissue samples of critically ill patients and by studying the effects of treatment allocation on the innate immune response and pathways of inflammation and autophagy.

